# A prospective single-center protocol for using near-infrared fluorescence imaging with indocyanine green during staging laparoscopy to detect small metastasis from pancreatic cancer

**DOI:** 10.1186/s12893-019-0635-0

**Published:** 2019-11-07

**Keywords:** Pancreatic cancer, Indocyanine green, Liver metastasis, Peritoneal metastasis, Staging laparoscopy

## Abstract

**Background:**

Pancreatic resection and radiotherapy are powerful tools in the multidisciplinary local treatment of pancreatic ductal adenocarcinoma (PDAC). However, 10–20% of patients with preoperatively resectable PDAC have radiographically occult metastases, which results in laparotomy without resection. This study aims to explore the utility of intraoperative near-infrared (NIR) imaging with indocyanine green (ICG) during staging laparoscopy to detect PDAC metastasis.

**Methods:**

This prospective study will evaluate patients with radiographically non-metastatic PDAC before they undergo planned pancreatic resection or chemoradiotherapy. Enrolled patients will receive ICG intravenously (0.5 mg/kg) before the staging laparoscopy. During the staging laparoscopy, the abdominal cavity will be observed using standard white-light laparoscopic imaging and then using NIR-ICG imaging. Suspicious lesions that are detected using standard imaging and/or NIR-ICG imaging will be examined intraoperatively using frozen sections and permanent specimens. We will evaluate the benefit of NIR-ICG imaging based on its ability to identify additional liver or peritoneal lesions that were not detected during standard white-light imaging.

**Discussion:**

This study will help establish the clinical utility of NIR-ICG imaging to more precisely identify metastases from radiographically non-metastatic PDAC. This approach may help avoid needless major surgery or radiotherapy.

**Trial registration:**

This protocol was registered on April 1, 2017 on the UMIN Clinical Trials Registry: UMIN000025900 and February 26, 2019 on the Japan Registry of Clinical Trials: jRCT1051180076.

## Background

Pancreatic ductal adenocarcinoma (PDAC) is the fourth leading cause of cancer-related death in Japan, and increasing incidences have been reported in Japan and Western countries. Pancreatic resection and radiotherapy are powerful tools in the multidisciplinary local treatment of PDAC. However, in patients with preoperatively resectable PDAC (R-PDAC), radiographically occult metastases are noted in 10–20% of cases, with the metastatic lesions typically being detected in the liver or peritoneum. Staging laparoscopy is thought to be helpful for identifying small metastases and for reducing the rate of non-therapeutic laparotomy [1]. Staging laparoscopy has also revealed metastatic lesions in approximately 20% of patients with radiographically locally advanced unresectable PDAC (LA-PDAC) [2].

Despite an extensive work-up with staging laparoscopy, some patients with localized PDAC also experience early progression with distant metastasis. Local treatments (e.g., resection or radiotherapy) may not be indicated in these cases, and a more accurate detection of radiographically occult metastases may help improve treatment selection for these PDAC patients. Intraoperative near-infrared (NIR) visualization using indocyanine green (ICG) reportedly improves the diagnostic accuracy for radiographically occult tumors of the liver or peritoneum in cases with hepatocellular carcinoma or colorectal cancer [3–5]. However, there is a paucity of information regarding the role of NIR-ICG imaging in the work-up for PDAC. Therefore, the protocol for this prospective study was designed to explore the clinical utility of NIR-ICG imaging during staging laparoscopy to detect PDAC metastasis.

## Methods

### Study design

This single-center prospective study will evaluate patients with radiographically R-PFAC or LA-PDAC before they undergo planned local treatment (pancreatic resection or chemoradiotherapy). Enrolled patients will receive ICG preoperatively and undergo staging laparoscopy with standard white-light imaging followed by NIR-ICG imaging at the Kobe University Hospital. The study protocol has been approved by the Ethics Committee at Kobe University Medical School Hospital (approval No: 290078) and the Kobe University Clinical Research Ethical Committee (approval No: C180070), and the study was opened in March 2018.

### Primary outcome

The primary outcome will be the ability of NIR-ICG imaging: the efficacy is defined as an identification at least one metastatic tumor that was not detected using standard white-light imaging. This outcome was selected based on a desire to obtain additional information that is not captured during standard imaging.

### Secondary outcome

The secondary outcome will be any change in treatment that was based on the findings from the NIR-ICG imaging.

### Study population

Planned local treatment (pancreatic resection or radiotherapy) for radiographically T3 or T4 (UICC) [6] tumors and written informed consent for staging laparoscopy are indications for staging laparoscopy.

#### Inclusion criteria

Patients will be included in the study if they fulfill the following criteria:
Age of ≥20 years and able to provide written informed consentPathological or clinical diagnosis of PDACRadiographically non-metastatic diseasePlanned for staging laparoscopy followed by a local treatment (pancreatic resection or radiotherapy).

#### Exclusion criteria

Patients will be excluded from the study if they fulfill any of the following criteria:
Allergic to iodinePregnancyChronic liver disease with the Child-Pugh class B or CRadiographically suspected malignant ascitesAnother malignancy within five years other than endoscopically cured digestive tract cancerInvestigator judgement that the patient should not participate for any reason

### Sample size

The target sample size is set to 40 patients in order to detect a significant difference in the primary outcome. Studies of NIR-ICG imaging for colorectal cancer have indicated that 10–43% of patients had additional metastases that were only identified using NIR-ICG imaging [7]. Thus, we conservatively assumed that NIR-ICG imaging would detect additional radiographically occult metastases in 10% of the cases. Thus, 7 patients would be needed to identify a significant difference in the primary outcome, based on a null hypothesis of 0% efficacy with a one-sided significance level of 2.5 and 80% power. Between April 2014 and June 2016, we retrospectively determined that the expected rate of radiographically occult PDAC metastases was approximately 20% at our center (26% of 72 historically study-eligible patients). Therefore, we calculated the required sample size to be 35 patients (7 / 0.2 = 35), and increased the sample size to 40 patients to account for 5 possible dropouts. Kobe University Hospital typically treats 20–30 patients per year who would be considered eligible for the study, which suggest that a sufficient number of patients may be enrolled during the recruitment period.

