#### *Statistical analysi*s

The subjects’ baseline characteristics will be reported using summary statistics and distributions. Nominal variables will be reported as number and proportion. Continuous variables will be reported as the number of subjects, mean and standard deviation values, as well as minimum, median, and maximum values. The primary outcome analysis will evaluate the proportion and 95% confidence interval for the identification of at least one additional metastatic tumor using NIR-ICG imaging. The hypothesis testing will be based on a single sample, a null hypothesis of 0% efficacy, and a one-sided significance level of 2.5%. Efficacy is defined as the identification of at least one metastatic tumor that was not detected using standard white-light imaging. “Metastatic tumor” is defined as a histologically diagnosed lesion with adenocarcinoma. The sensitivity and specificity of white-light imaging and NIR-ICG imaging will be investigated. Safety outcomes will be evaluated using the proportion and two-sided 95% confidence interval based on a binomial distribution.

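### Seven patients do not give the stated 80% power: at a 10% detection rate the exact power is 52%, and 80% needs 16

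*Protocol article*

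**What the plan says.** The Sample size section of the protocol article builds the target in three steps.

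- **Effect size.** From colorectal studies the authors write that "we conservatively assumed that NIR-ICG imaging would detect additional radiographically occult metastases in 10% of the cases".
- **Core number.** "Thus, 7 patients would be needed to identify a significant difference in the primary outcome, based on a null hypothesis of 0% efficacy", and the sentence continues "with a one-sided significance level of 2.5 and 80% power". The percent sign after 2.5 is missing here. The Statistical analysis section supplies it and confirms a single-sample test against 0%.
- **Scaling.** The authors report that "the expected rate of radiographically occult PDAC metastases was approximately 20% at our center (26% of 72 historically study-eligible patients". They then say "we calculated the required sample size to be 35 patients (7 / 0.2 = 35), and increased the sample size to 40 patients", the last five patients being an allowance for dropouts.

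A success is defined per patient: at least one histologically confirmed metastasis that white-light imaging missed. The article names no formula, exact test or software.

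**The concern.** A null of exactly 0% allows no successes at all, so one success refutes it and none cannot. Power is then simply the chance of seeing at least one success. With seven patients and a 10% chance each, only 0.7 successes are expected, so an 80% chance of at least one is not plausible.

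This is the only power statement in the article, and the enrolment target is derived from it. If the study ends with no NIR-only detection, a reader who trusts the stated power would take that as fairly strong evidence against a 10% rate. With seven patients of the intended kind, that outcome would be almost as likely as not even if the 10% assumption were true.

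**Working it through.** **Inputs** (Sample size and Statistical analysis sections): null rate p0 = 0; assumed rate p1 = 0.10; one-sided α = 0.025; power 0.80; core n = 7; occult-metastasis rate 0.20 (26% of 72 observed); scaled n = 35; enrolled n = 40.

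**1. Reproducing the 7.** The one-sample normal approximation is

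n = [z(1−α)·√(p0(1−p0)) + z(power)·√(p1(1−p1))]² / (p1 − p0)²

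With p0 = 0 the first term vanishes:

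n = [1.96 × 0 + 0.8416 × 0.30]² / 0.10² = 6.37, rounded up to 7.

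The stated figure is reproduced, and α plays no part in it. The other versions tried do not give 7: alternative variance in both terms 71, continuity correction 15, arcsine 19, exact binomial 16. The formula is an inference, since the article names none. Nothing below depends on it.

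**2. Exact power at n = 7.** Under p0 = 0 the rule that rejects on one or more successes has type I error 0. No test that declines to reject on zero successes can be more powerful. Its power is 1 − (1 − p)^n.

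| n | Exact power at p = 0.10 |
|---|---|
| 7 | 1 − 0.9^7 = 52.2% |
| 15 | 1 − 0.9^15 = 79.4% |
| 16 | 1 − 0.9^16 = 81.5% |

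The shortfall at n = 7 is about 28 percentage points. Seven patients would give 80% power only if the true rate were 1 − 0.2^(1/7) = 20.5%, about twice the assumed rate.

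**3. Carrying it through the plan's own scaling.** The plan has 7 / 0.2 = 35. With the exact number this becomes 16 / 0.2 = 80 before dropouts.

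**4. What 35 or 40 patients give.** This depends on what the 10% is a proportion of.

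| Reading of the 10% | Success rate per enrolled patient | Power at 35 | Power at 40 |
|---|---|---|---|
| Of patients with occult metastasis, occult rate 20% | 0.20 × 0.10 = 2.0% | 1 − 0.98^35 = 50.7% | 1 − 0.98^40 = 55.4% |
| Of patients with occult metastasis, occult rate 26% | 0.26 × 0.10 = 2.6% | 1 − 0.974^35 = 60.2% | 1 − 0.974^40 = 65.1% |
| Of all enrolled patients | 10% | 1 − 0.9^35 = 97.5% | 1 − 0.9^40 = 98.5% |

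The column for 40 assumes no dropouts. The column for 35 assumes the five that the plan allows for.

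**The case against.** The strongest reply is that an error in the intermediate figure 7 is not an error in the trial of 40. The analysis population is everyone who completed laparoscopy and NIR-ICG imaging, the endpoint is a per-patient proportion, and the colorectal range behind the 10% is also given per patient. If the 10% is a rate among all enrolled patients, 40 patients give 98.5% power and the study is amply sized.

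The wording does leave this open, and the reading matters a great deal for the trial as a whole. It does not rescue the statement, however. If the 10% already refers to all patients, dividing by 0.2 has no rationale. If it refers to patients with occult metastasis, as the division implies, power at 40 is 55% to 65%. On neither reading do seven patients give 80%.

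Two lesser points have some weight. First, the formula behind the 7 is inferred. Second, the article calls the study exploratory and plans a proportion with a 95% confidence interval, which stays interpretable whatever the power. Yet the article also justifies 40 as the number needed to detect a significant difference and specifies a formal test, so the stated power has to be correct.

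**Conclusion.** The concern holds. At the assumed 10% rate and against a 0% null, seven patients give at most 52.2% power, and 80% first requires 16. This follows from the binomial distribution with independent patients and from a test that cannot reject on zero successes; it needs no assumption about the formula the authors used.

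The effect on the whole trial rests on one further assumption, the denominator of the 10%. On the reading implied by the plan's scaling, the design falls 15 to 25 points short of 80% at 40 patients without dropouts (65.1% and 55.4%), and 80 evaluable patients would be needed at a 20% occult rate. On the all-patients reading the trial is not underpowered, but the derivation printed in the article is not the one that supports it.

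**What to change.** Rewrite the sample size paragraph as follows.

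1. Remove the claim that seven patients give 80% power.
2. State whether the 10% is a proportion of patients with occult metastasis or of all analysed patients. Drop the division by 0.2 if it is the latter.
3. Give the exact probability of at least one NIR-only metastasis, 1 − (1 − p)^n, at the planned size with and without the five dropouts. The values are 50.7% and 55.4% at 2.0% per patient, 60.2% and 65.1% at 2.6%, and 97.5% and 98.5% at 10%.
4. Alternatively, or in addition, justify 40 by the precision of the exact 95% confidence interval already central to the primary analysis. For example, with no successes in 40 the two-sided upper limit is 1 − 0.025^(1/40) = 8.8%.

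The cost is one corrected paragraph in the protocol and, where it is repeated, in the SAP. The planned 40 can stand, with no change to endpoint or analysis. On the reading that the present scaling implies, the price is a less favourable stated power.

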### Analysis methods

#### Analysis population

The analysis dataset will include data from all enrolled participants who completed the staging laparoscopy, but without data from patients who withdrew their informed consent or did not complete the NIR-ICG imaging for any reason.

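### The stated 80% power does not hold on either reading of the assumed 10% detection rate: exact power at 35–40 patients is about 51–55% or 97.5–98.5%

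*Protocol article*

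**What the plan says.** In the protocol article, Sample size, the assumption is that "NIR-ICG imaging would detect additional radiographically occult metastases in 10% of the cases". It is drawn from colorectal cancer studies whose range, 10–43%, is given per patient. From it the plan obtains 7 patients, "based on a null hypothesis of 0% efficacy with a one-sided significance level of 2.5 and 80% power".

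The plan then puts the rate of radiographically occult metastasis at "approximately 20% at our center (26% of 72 historically study-eligible patients") and continues: "Therefore, we calculated the required sample size to be 35 patients (7 / 0.2 = 35"). Five possible dropouts bring the target to 40.

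Under Analysis population, "The analysis dataset will include data from all enrolled participants who completed the staging laparoscopy", less those who withdrew consent or did not complete the near-infrared imaging. Nothing limits the set to patients with occult metastasis. Under Statistical analysis, the primary result is a proportion with a 95% confidence interval, and "The hypothesis testing will be based on a single sample, a null hypothesis of 0% efficacy, and a one-sided significance level of 2.5"%.

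**The concern.** Two things in the Sample size paragraph need checking.

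- **The 7.** Seven patients at a 10% rate yield 0.7 expected successes. That is too few for an 80% chance of seeing even one.
- **The denominator.** The source range is per patient, which suggests that 10% is a rate among all patients. Dividing by 0.2 makes sense only if the 7 are patients with occult metastasis, so that 10% is a rate within that subgroup. The analysis set is all patients, and the plan never states the proportion it expects there.

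The stake is the power claim for the primary outcome. If the expected proportion is 2%, a benefit of the assumed size would leave no trace in about half of such trials. If it is 10%, the trial is much better powered than stated. A reader cannot tell which, and will probably judge the result against 10%.

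**Working it through.** **Inputs.** From Sample size: null rate 0%, one-sided 2.5%, target power 80%, assumed rate 10%, prevalence 20% (26% observed in 72 patients), 35 analysed after 5 dropouts from 40. From Analysis population: the denominator is all patients who completed laparoscopy and near-infrared imaging.

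**1. Reproducing the plan's 7.** The one-sample normal approximation is

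n = [(z₀.₉₇₅·√(p₀(1−p₀)) + z₀.₈₀·√(p₁(1−p₁))) / (p₁ − p₀)]².

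With p₀ = 0 the first term vanishes, so the significance level no longer enters:

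n = 0.8416² × (0.10 × 0.90) / 0.10² = 0.7083 × 9 = 6.37, rounded up to 7.

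Then 7 / 0.2 = 35 and 35 + 5 = 40. The plan's figures reproduce.

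**2. Exact power.** Under a 0% null no success can occur, so one success rejects (type I error 0) and power = 1 − (1 − p)^n. No test that refuses to reject on zero successes can do better.

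- 7 patients at 10%: 1 − 0.9⁷ = 52.2%, not 80%.
- Exact n for 80% at 10%: 1 − 0.9¹⁵ = 79.4% and 1 − 0.9¹⁶ = 81.5%, so 16.

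**3. Power over the analysis set, by reading of the 10%.**

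| Reading | Rate over all analysed patients | Power, n = 35 | Power, n = 40 | n for 80% |
|---|---|---|---|---|
| Within occult metastasis, prevalence 20% | 0.10 × 0.20 = 2% | 1 − 0.98³⁵ = 50.7% | 1 − 0.98⁴⁰ = 55.4% | 80 |
| Within occult metastasis, prevalence 26% | 0.10 × 0.26 = 2.6% | 1 − 0.974³⁵ = 60.2% | 1 − 0.974⁴⁰ = 65.1% | 62 |
| Among all patients | 10% | 1 − 0.9³⁵ = 97.5% | 1 − 0.9⁴⁰ = 98.5% | 16 |

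The plan expects 35 analysed patients, so the n = 35 column is the planned power; n = 40 applies only with no dropouts.

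**4. Where the loss arises.** The approximation in step 1, applied directly at 2%, gives 0.7083 × 0.98 / 0.02 = 34.7, rounded up to 35. The all-patient and subgroup routes therefore agree on 35. Their exact powers are also close (52.2% for 7 at 10%, 50.7% for 35 at 2%), because patients without metastasis cannot be successes. The exact subgroup number scaled the same way is 16 / 0.2 = 80, matching the table. The shortfall comes from the approximation, not from dividing by prevalence.

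**5. Prevalence.** 26% of 72 is 18.7, about 19 patients. 7 / 0.26 = 26.9, so 27. Using 20% enlarges the sample, but the plan does not say that it was chosen for that reason.

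**The case against.** The best defence has four parts.

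- **The scaling is legitimate.** Dividing a subgroup requirement by prevalence is ordinary practice, and a 10% subgroup rate is compatible with a 2% rate overall. This stands. A reader might infer that the division itself costs the power, or that 35 follows from no reading of the 10%. Neither is supported: 35 follows on the subgroup reading once the approximation is accepted.
- **The plan never states 2%.** This also stands. A reader might conclude that the trial is simply underpowered at 51–55%. The documents do not settle that: the per-patient source range favours 10% of all patients, while the division favours the subgroup. On the all-patient reading there is no shortfall, and the stated 80% is too low.
- **Rounding 26% down to 20% is cautious.** True: it did not shrink the sample, so it is a matter of wording.
- **The study is exploratory**, as the section on data monitoring and auditing says, and the proportion and its interval will be reported whatever the power. This softens the consequence but does not remove the error. The Sample size section says the number was set to show a significant difference with 80% power, and the analysis section fixes a test at one-sided 2.5%. A power figure that is stated should be correct.

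**Conclusion.** The point holds. The 80% power is wrong as stated, and the cause is a normal approximation that breaks down at a null of 0%. On the reading that the division implies, planned power is 50.7% (55.4% with no dropouts; 60.2% and 65.1% at 26% prevalence). On the reading that the cited range suggests, it is 97.5% (98.5% with no dropouts), and the division has no basis. The undefined denominator decides which applies.

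This rests on the plan's own 10%, 20% and 26%, on independent patients, and on rejection with one success. The article does not name the test. A rule needing more than one success would have lower power on both readings. It does not follow that 40 patients are too few for the study: that depends on which reading was meant and on whether 80% power is required.

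**What to change.** Rewrite the Sample size paragraph and keep 40 patients.

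1. State whether the 10% is among patients with occult metastasis or among all patients, and give the resulting expected proportion over the analysis set (2%, 2.6% or 10%). If it is among all patients, drop the division by 0.2.
2. Replace the 7 patients and the 80% power with exact binomial power at 35 and 40 for that proportion: about 51–55% at 2%, or 97.5–98.5% at 10%. Restating the rate without changing the method would not help, since the same approximation returns 35 at 2%.
3. Add the exact 95% confidence interval at the matching expected count. At 10%, 40 × 0.10 = 4, and 4/40 gives 2.8–23.7%. At 2%, 40 × 0.02 = 0.8, so show the interval for 0 or 1 success. For 0/40 the exact upper limit is 1 − 0.025^(1/40) = 8.8%.
4. Say whether 20% is a deliberately cautious rounding of the observed 26%.

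The cost is one paragraph, with no change to the sample size or the analysis. The downside is that the stated power may become less favourable. If the sponsor means 2% and also wants 80% power, 40 patients cannot deliver it, and the size should be presented as a choice of feasibility or precision.

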### Staging laparoscopy (intervention)

Enrolled patients will receive ICG intravenously (0.5 mg/kg) on the day before staging laparoscopy. During staging laparoscopy, peritoneal washing cytology (PWC) sample from the pelvis with 100 ml of normal saline is collected at first. The abdominal cavity will be observed using standard white-light laparoscopic imaging and then using NIR-ICG imaging. Suspicious lesions that are defined as detectable nodules under white-light imaging or NIR-ICG imaging on the liver or peritoneum, will be examined intraoperatively using frozen sections and permanent specimens. If more than five suspicious lesions are observed on the individual organs (liver and peritoneum), we will examine five lesions using frozen sections for each organ, and additional specimens of the frozen sections will be taken when all specimens are diagnosed as benign lesions in the first examination. We will resect up to ten lesions for each organ.

The findings will be evaluated intraoperatively by the entire operative team (two or three surgeons) and at least one other surgeon will postoperatively review the recorded video. We have defined the benefit of NIR-ICG imaging as the identification of additional liver or peritoneal lesions that were not identified during the standard white-light imaging. The final judgement will be based on consensus among the operative surgeons.

Each lesion that was taken during staging laparoscopy is examined using standard white-light imaging, NIR-ICG imaging, and histological finding to detect for positive or negative lesions. False positive or negative detection with white-light imaging and NIR-ICG imaging is recorded according to the confirmed findings of staging laparoscopy and histological diagnosis.

The staging laparoscopy will be performed using a laparoscopic high-definition fluorescence imaging system (Karl Storz GmbH & Co. KG, Tuttlingen, Germany). The system includes light sources for white-light and 760-nm light, as well as a 30° 10-mm laparoscope containing optical filters. The system allows the surgeon to easily switch between the white-light and NIR sources using a foot pedal.

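### Whether white light missed a metastasis is settled by the team that has also made the NIR pass, so second-look finds can be credited to ICG

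*Protocol article*

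**What the plan says.** All of the relevant procedure is in the Protocol article, section Staging laparoscopy (intervention).

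- **Order.** "The abdominal cavity will be observed using standard white-light laparoscopic imaging and then using NIR-ICG imaging". The order is the same for everyone. The article describes no second white-light look and no comparison group.
- **Assessors.** The operating team of two or three surgeons evaluates the findings during surgery, and "at least one other surgeon will postoperatively review the recorded video".
- **Decision.** "The final judgement will be based on consensus among the operative surgeons".
- **Benefit.** NIR-ICG is credited with the "identification of additional liver or peritoneal lesions that were not identified during the standard white-light imaging". Primary outcome and Statistical analysis turn this into a per-patient endpoint: at least one metastatic tumour that white light did not detect.
- **What counts as suspicious.** "Suspicious lesions that are defined as detectable nodules under white-light imaging or NIR-ICG imaging on the liver or peritoneum". A nodule seen under either light qualifies, so fluorescence is not required.
- **Safeguards.** A metastatic tumour "is defined as a histologically diagnosed lesion with adenocarcinoma" (Statistical analysis). Each lesion taken is also classed as positive or negative under white light, under NIR-ICG and on histology, and false positives and false negatives of both modes are recorded.

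Statistical analysis tests the proportion against 0% at a one-sided 2.5% level.

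**The concern.** The endpoint has two parts: the lesion is a metastasis, and white light did not detect it. Histology settles the first. The second is a judgement, and the article gives it to surgeons who by then have also made the NIR pass.

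A second inspection of the same abdomen can turn up an overlooked nodule under any light. With a fixed order and no repeat white-light look, the design cannot separate what ICG reveals from what looking twice reveals. The second-look part can only add to the yield. Two other planned results depend on the same attribution: the sensitivity of white light, and the secondary outcome of treatment changes due to NIR-ICG findings. The Discussion section intends the result to establish the clinical utility of NIR-ICG imaging, which is a claim about the modality and not about a second look.

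**Working it through.** **1. The plan's own figure.** Sample size gives 7, then 35, then 40. The one-sample normal approximation with p0 = 0, p1 = 0.10, one-sided 2.5% and 80% power is

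n = [z(0.975)·√(p0(1−p0)) + z(0.80)·√(p1(1−p1))]² / (p1−p0)² = [0 + 0.8416 × 0.3]² / 0.01 = 6.37, rounded up to 7.

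Then 7/0.2 = 35 and 35 + 5 = 40. The figures reproduce. The significance level drops out because the null variance is zero.

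**2. What one misattributed patient does.** Under p0 = 0 the probability of any success is 0, so one credited patient rejects. One success in 40 has an exact 95% interval of 0.06% to 13.2%, which excludes 0. Whatever the null, one misattributed patient moves the estimated yield by 1/40 = 2.5 percentage points.

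**3. Illustration of size.** Let q be the proportion of patients in whom a second look alone, with no contribution from ICG, finds a confirmed metastasis that is then credited to NIR-ICG. The documents give no value for q, so the values below are assumptions. The chance of at least one credited patient is 1 − (1−q)^n.

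| q (assumed) | Share of the 20% with occult metastases | n = 35 | n = 40 |
|---|---|---|---|
| 0.5% | 2.5% | 16% | 18% |
| 1% | 5% | 30% | 33% |
| 2% | 10% | 51% | 55% |
| 5% | 25% | 83% | 87% |

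Example: 1 − 0.98^40 = 0.554. The second column is q/0.20, using the occult-metastasis rate in Sample size.

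**4. How much of this comes from the 0% null.** If two credited patients were needed among 40, the chances at q = 1%, 2% and 5% would be 6%, 19% and 60%. The zero null therefore amplifies the effect but does not create it.

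**5. Can the stated safeguards separate the two sources?** Consider a true metastasis overlooked on the first pass, noticed during the NIR pass, and visible when the light is switched back.

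- If white-light status is taken from the first pass, the lesion is white-light negative and counts for NIR-ICG.
- If it is taken from re-inspection, the lesion is white-light positive and does not count.

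The wording of the benefit definition points towards the first pass. The statement that each lesion taken is examined under both lights could mean either. The two readings can give opposite primary results for the same patient, and the same surgeons choose between them case by case.

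**The case against.** The strongest reply is that white light followed by NIR is the right order for the question asked, namely what NIR-ICG adds to standard imaging. Reversing the order would contaminate the white-light reading. Credit requires adenocarcinoma on histology, so benign nodules cannot inflate the yield, and white-light status is recorded for each lesion. Data monitoring and auditing calls the study exploratory. The timing of lesion logs and the order of video reading are details that a condensed article may leave to the full protocol.

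Much of this stands. The order is defensible, histology is a real safeguard, and a locked list may exist in a document not shown. The objection does not remove the stated rule that the operating team's consensus decides, or the unclear source of white-light status.

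A reader might infer more than the article supports:

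- **That the video review is independent and disregarded.** The article says only that another surgeon reviews the video. It gives that review no stated role and does not exclude it from the deliberation.
- **That the team knows the frozen-section result when it decides, or makes a less careful first pass because NIR follows.** Neither is stated.
- **That every lesion plainly visible on white light still counts for NIR-ICG.** Per-lesion recording could prevent this; the text leaves it open.
- **That the 18% with unresectable disease at later laparotomy (Discussion) shows that metastases are often overlooked.** That figure is not limited to metastases, and laparotomy is a different examination from a second laparoscopic look.

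**Conclusion.** The concern holds as a weakness in how the primary outcome is adjudicated. The element that decides the endpoint is left to the consensus of surgeons who have made both passes, the other surgeon's review has no stated role, and the source of a lesion's white-light status is not fixed. The resulting bias in the yield is upward.

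Its size cannot be set from the documents. The 18% to 87% range at n = 40 rests on assumed second-look yields of 0.5% to 5% of patients and on the 0% null, under which one credited patient is enough. It should not be read as an estimate of the actual false-positive rate. The upper end would need a second look alone to yield a metastasis in a quarter of the patients with occult metastases. Even the lowest value shown is well above the nominal 2.5%. The change is worth making because it is cheap and bears on the primary result.

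**What to change.** 1. Record and lock the white-light lesion list in the case report form before switching to NIR. Define non-detection by white light for the primary outcome from that list, not from later consensus. This fixes the source of the status and removes hindsight, but it does not by itself remove the second-look effect. Steps 2 and 3 address that.
2. Have the video reviewer who is already planned read the white-light segment first, masked to the NIR segment and to histology. As a sensitivity analysis, report the yield without lesions that this reviewer calls on white light. Making the reviewer's call a veto on the primary outcome is not proposed. It would change the question from what the live team missed to what neither the team nor a later reader saw.
3. For each lesion first noted under NIR, switch back and record whether it is visible on white light. The equipment already permits this: "The system allows the surgeon to easily switch between the white-light and NIR sources using a foot pedal". Report white-light-visible and fluorescence-only lesions separately. The visible ones should not simply be discarded, because fluorescence may have drawn attention to them.

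The cost is one page in the case report form, a fixed reading order for a review already planned, and possibly a lower reported yield.
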